## Abstract

**Background:**

Community health workers (CHWs) are effective in delivering behavioral activation (BA), especially in low-resource settings. In an area with a lack of Spanish-speaking mental health counselors, such as southwest Montana, CHWs can provide needed care.

**Objective:**

The goal of this pilot study protocol is to test the feasibility, acceptability, and preliminary efficacy of a model of care that engages CHWs as providers of BA.

**Methods:**

We will train 2 CHWs in BA methodology. We will enroll 20 participants who screen positive for depression in a 12-week telephone intervention for BA. Preliminary efficacy will be tested in pre- and postscores of the Beck Depression Inventory and semistructured interviews. Feasibility and acceptability will be measured through participant retention and treatment adherence. The Therapeutic Alliance with Clinician Scale will be used to measure the strength of the therapeutic relationship. Descriptive statistics will measure alliances and repeated measures ANOVA will measure trends and changes in depression scores.

**Results:**

Enrollment began in October 2023. A total of 12 participants completed at least 10 BA sessions and all study measures by the time the study concluded in May 2024. In August 2024, data analysis occurred with an anticipated manuscript to be submitted for publication in October 2024.

**Conclusions:**

Results from this study will inform future studies into the implementation of an evidence-based mental health intervention in a limited resource setting for Latino people with limited English proficiency.

**International Registered Report Identifier (IRRID):**

DERR1-10.2196/57343

## Introduction

### Background

Latino people with limited English proficiency (LEP) experience persistent and preventable mental health disparities. According to the National Alliance on Mental Illness, 18% of Latino people in the United States have a mental illness, but only 33% of those received professional services (compared to 50% of non-Hispanic Whites with mental illness) [1]. In Montana and other Mountain West regions with rapidly increasing LEP populations, the mental health infrastructure has not kept pace with the growing need. Existing English-speaking providers are only able to meet 11% of the need in rural and frontier counties of Montana [2]; however, in Montana counties where the LEP population has grown by as much as 200% [3], access to culturally and linguistically congruent mental health providers is even more dire. Through 3 years of data collection using a community-engaged approach, our team found depression in 15% of the LEP population [4]. Working with a community advisory board, we found the primary mental health concern of the LEP community to be depression and a lack of Spanish-speaking providers [5]. Montana leads the nation in suicide rates [6], making access to mental health services an urgent concern.

An evidence-based approach to increasing mental health services is the use of community health workers (CHWs) who can be specially trained to deliver mental health interventions [7]. CHWs are generally from the same community as the population they work with, and while traditional models leverage their ability to provide a bridge to health and other resources, CHWs can provide evidence-based treatments (EBTs), including preventive care and early interventions in low-resource settings, capitalizing on their language and cultural skills [8]. Evidence suggests that CHW-provided EBTs produce mental health outcomes that are comparable to professionally delivered treatments [9]. In an area with a lack of Spanish-speaking mental health counselors, such as southwest Montana, CHWs can provide much-needed services. Indeed, in preliminary work by our team, we found improvements in depression scores in patients who engaged in 6 telehealth motivational interviewing sessions with a trained CHW (Montana State University, unpublished).

CHWs have a positive impact on health outcomes and the ability to address disparities in mental health treatment in a cost-effective, community-focused way. This is especially important in a low-resource setting with a lack of Spanish-speaking providers. Therefore, the goal of this study is to test the feasibility and acceptability of a model of care that engages CHWs as providers of the evidence-based mental health intervention of behavioral activation (BA).

### Previous Studies

The theoretical underpinnings of BA suggest that depression results when a person disengages from pleasurable activities and experiences a negative mood [10]. To combat this, the BA protocol helps a client identify activities that provide pleasure and increase positive feelings. Practitioners assist the client to target core problems by scheduling specific activation activities assigned as homework [11]. Persons in BA participate in activities that are enjoyable and monitor their mood while engaging in these activities to increase their awareness of how the activity influences their mood [12]. Clients learn the connections between their activities and their moods and schedule activities to help increase engagement in activities that create positive moods [13]. Clients are also taught to identify behaviors that interfere with their goals (“depressed behaviors”) and learn ways to replace these behaviors with positive ones [14]. BA allows clients to explore personal values and goals and to identify positive behaviors that are consistent with meeting those goals. Pleasurable activities are scheduled into the daily routine, and the client tracks mood changes in response to those activities. Clients are also supported in identifying persons who may help support them in accomplishing these activities [15].

Research shows BA is an effective intervention to address depression in Latino people with LEP when delivered by Spanish-speaking mental health professionals. In a randomized hybrid efficacy and effectiveness trial, Kanter and colleagues [11] saw increased engagement and retention from the intervention group receiving BA versus the treatment-as-usual group. In another efficacy study, Latino patients diagnosed with major depressive disorder experienced a greater reduction of depressive symptoms with the implementation of BA-centered treatment when compared to treatment as usual [16]. Other comparable studies found similar results when comparing BA to treatment as usual [17,18].

However, studies on the effect of BA delivered by CHWs are limited. In one study, Magidson and colleagues [19] successfully implemented BA treatment for torture survivors in Iraq with the use of CHWs to deliver the intervention. The procedure was modified to include relevant cultural elements and account for low literacy, and researchers saw improvements in depression. A total of 2 pilot studies—one with veterans and another including the target population (US Latino people)—reported efficacy and fidelity with the use of CHWs as the public-facing component of a multidisciplinary care team [20,21].

This study will address the gap in the existing science of the effect of CHW-delivered BA intervention on depression among Latino people with LEP by testing its acceptability, feasibility, and preliminary efficacy. We will also address a disparity in mental health outcomes for Latino people with LEP in southwest Montana by increasing the supply of Spanish-language mental health resources.

## Methods

### Intervention

In total, 2 bicultural/bilingual CHWs will be recruited and trained in the administration of BA through the University of Washington’s Advancing Integrated Mental Health Solutions Center. The training, specifically designed for CHWs and other patient-facing practitioners, consists of 8 hours of training over the course of 4 months and includes both web-based asynchronous work and 5 hours of web-based training sessions with the BA professional. CHWs learned the principles of BA, how to help participants identify rewarding activities and apply activity scheduling, and how to evaluate progress. The CHWs will be supervised by a nurse who has been trained in supervising CHWs for the duration of the study. As needed, a licensed professional counselor, well versed in working with the Latino population, will be available for further supervision and case management support.

The trained CHWs will deliver a 12-week program of BA over the phone. Individual 50-minute sessions will be scheduled based on participant preference and will consist of creating a plan of activation activities, self-monitoring, identifying avoidance behaviors, setting goal-oriented behaviors, and recording mood changes with activation activities [22]. During sessions, CHWs will discuss the cycle of depression and how activities influence moods. Together, CHWs and participants will identify participant goals, create “activating” activities that help work toward those goals, and develop strategies to schedule pleasurable activities. Participants will employ identified activities as homework and track their moods with a daily log. CHWs will record participant progress, homework, and changes in mood in REDCap (Vanderbilt University).

### Participants

We aim to recruit 20 participants for this pilot study. Recruitment will occur through a variety of community-based means: in-person community health screening events conducted by our team in Southwest Montana, referrals from the federally qualified health center (Community Health Partners) and the Gallatin City-County Health Department [4], contacts with nonprofit and service providers who work with the Latino population, and word of mouth through our community advisory boards and previous research partners. Eligible participants will be monolingual Spanish speakers with a score of at least 5 on the Patient Health Questionnaire-9 and who have the ability to participate in a phone intervention. The exclusion criteria will include current treatment by a behavioral health specialist and proficiency in English. The study enrollment goal will be 20 with an anticipated attrition rate of 20%, for a final n=16. Studies with attrition rates higher than 20% may be influenced by attrition bias [23]. Participants will be randomly assigned to one of 2 CHWs, so that each will manage a caseload of 10 participants (Figure 1). Participants will schedule their own sessions with the CHW and do not have to meet weekly. Participants who complete 10 of the 12 sessions will be considered to have completed the interventions.

**Figure 1 figure1:**
[figure not shown]
Proposed recruitment. CHW: community health worker; PHQ9: Patient Health Questionnaire-9.

### Data Collection and Analysis

We will use a mixed-methods approach to determine the acceptability, feasibility, and preliminary efficacy of the intervention. Acceptability will be measured through participant retention (number of total sessions completed of 12) and treatment adherence (percent of homework assignments completed). We will also use the Therapeutic Alliance with Clinician Scale, a 9-item Likert scale used to estimate the strength of the therapeutic relationship [24]. It has been validated in a Spanish-speaking population with an internal consistency of 0.96 [25]. Descriptive statistics will be used to determine alliance, with higher scores signaling higher estimates of alliance.

The goal of analyzing feasibility is to determine factors that contributed to the implementation of the study. For example, if the attrition rate exceeds 20%, the retention rate in the study would suggest low feasibility for participation. We will assess our methods, including participant recruitment and retention, and test the acceptability of study questionnaires. We will do this through a quantitative analysis of the counts of the number of participants who express interest versus those who enroll versus those who complete the BA sessions. One month after the study concludes, we will conduct qualitative interviews with both CHWs and a subset of participants (expected n=8). Participants who complete at least 1 session will be randomly selected by a research assistant, who will conduct interviews via telephone using a semistructured interview guide. Interviews will be audio recorded and transcribed in Spanish. We will analyze Spanish transcripts through thematic analysis [26]. Potential questions will include how participants heard about the study and why they decided to join, what aspects of the study made it easy or difficult to participate (including reasons for not completing any sessions), facilitators and barriers to completing study questionnaires, and recommendations for improvement to the study protocol. Study measures are shown in Table 1.

**Table 1 table1:** Study implementation measures.

Outcome	Measurement	Analysis
Acceptability	Participant retention	Total sessions completed/12
	Treatment adherence	Percentage of homework assignments completed
	Therapeutic Alliance with Clinician Scale	Descriptive statistics
Efficacy	Beck Depression Inventory-II	Linear regression with repeated measures
Feasibility	Qualitative interviews	Thematic analysis

We will measure preliminary efficacy in 2 ways. First is through the semistructured interviews. We will ask participants what effect the intervention had on their general mood and if they felt the study helped improve their depression. We will also measure changes in depressive scores through the Beck Depression Inventory-II [27]. This 21-item self-report inventory is widely used to measure depression severity and has been tested in Spanish with internal consistency between 0.91 and 0.95 [28]. We will administer the Beck Depression Inventory-II at baseline, after 3 sessions, after 6 sessions, after 9 sessions, and upon completion of the BA intervention. We will use repeated measures ANOVA to estimate the trends or changes in depression scores over treatment.

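### Interviews are drawn only from participants with at least one session, so the planned question on why people completed none cannot be put to anyone it concerns

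*Protocol article*

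**What the plan says.** All of this is in the Protocol article, Methods.

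- **Who is interviewed** (Data Collection and Analysis): one month after the study concludes, "we will conduct qualitative interviews with both CHWs and a subset of participants (expected n=8"). The participants are chosen as follows: "Participants who complete at least 1 session will be randomly selected by a research assistant".
- **What they are asked** (same paragraph): the potential questions cover "what aspects of the study made it easy or difficult to participate (including reasons for not completing any sessions"), along with recruitment, the questionnaires and suggestions for the protocol.
- **Other feasibility data** (same paragraph): attrition above 20% is read as low feasibility, and there are "counts of the number of participants who express interest versus those who enroll versus those who complete the BA sessions".
- **Table 1**: the Feasibility row lists only the interviews, analysed thematically.
- **Planning figures** (Participants): "The study enrollment goal will be 20 with an anticipated attrition rate of 20%, for a final n=16". Completion is defined thus: "Participants who complete 10 of the 12 sessions will be considered to have completed the interventions".

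**The concern.** The selection rule and the interview topic stand in one paragraph and do not fit together. A person who enrolled and never had a session is the only one who can say at first hand why no session took place, and the rule leaves that person out. This is not a detail that an article would leave to a fuller document, because the article states both the frame and the question.

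The section says that feasibility analysis is meant to identify what contributed to implementation, and it treats loss of participants as a sign of low feasibility. The reasons for loss are thus part of what the pilot sets out to learn. For people who never started, the plan provides no first-hand source of those reasons.

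**Working it through.** **1. Frame against question.** Enrolled participants fall into three groups by number of sessions.

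| Sessions completed | Can be drawn for interview? | Can answer why no session was completed? |
|---|---|---|
| 0 | No | Yes |
| 1 to 9 | Yes | No |
| 10 to 12 | Yes | No |

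No row has yes in both columns.

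**2. Other sources of reasons.** The counts run from interest to enrolment to completion. They give numbers, not reasons, and they do not separate non-starters from people who stopped part-way. Both community health workers are interviewed, but on non-starters their account would be second-hand. The article describes no other collection of reasons from people with zero sessions.

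**3. The plan's own figure.** 20 × (1 − 0.20) = 16, which reproduces the stated final n. That figure is not in dispute.

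**4. Effect of opening the frame.** The article does not say how many enrolled people would have zero sessions. Call this number k. It is an assumption, taken here from 1 to 4, where 4 = 20 − 16 would be the whole of the anticipated attrition. As written, the chance that 8 interviews include a non-starter is 0 for every k. With a simple random draw of 8 from all 20, the chance is 1 − C(20 − k, 8)/C(20, 8), with C(20, 8) = 125,970, and the expected number is 8k/20.

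| k | C(20 − k, 8) | Chance as written | Chance, all 20 eligible | Expected number, all 20 eligible |
|---|---|---|---|---|
| 1 | 75,582 | 0 | 0.40 | 0.4 |
| 2 | 43,758 | 0 | 0.65 | 0.8 |
| 3 | 24,310 | 0 | 0.81 | 1.2 |
| 4 | 12,870 | 0 | 0.90 | 1.6 |

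Opening the frame removes the contradiction, but a simple random draw could still miss a small group of non-starters. Sampling within strata avoids that, provided that they can be reached.

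**The case against.** **The wording may be loose.** The phrase is a parenthesis in a list of potential questions, and it could mean reasons for missing any of the sessions. People with 1 to 9 sessions could answer that. This reading is possible. On it the frame can stay, but the phrase needs rewording, so a correction is due either way.

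**Random selection is defensible.** It guards against hand-picked interviewees, and requiring one session makes sense for questions about the effect of the intervention. Both points stand. The fix keeps random selection within strata and keeps the one-session condition for those questions.

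A reader might also infer more than the documents support:

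- *That acceptability will look too good.* Acceptability is measured by sessions completed, homework completed and the therapeutic alliance scale. Who is interviewed does not alter these.
- *That perceived benefit will be inflated by leaving out non-starters.* Someone with no session received no intervention and has no effect on mood to report.
- *That feasibility rests on the interviews alone.* This is true of Table 1, but the text adds the attrition threshold and the counts, which register losses whoever is interviewed.
- *That early leavers are left out.* Anyone with 1 to 9 sessions is eligible. They could be missed by chance, but how likely that is depends on an assumed split. With 16 completers and 2 early leavers in a frame of 18, the chance that 8 interviews include no early leaver is 12,870/43,758 = 0.29; with 4 in a frame of 20 it is 12,870/125,970 = 0.10. The Results section reports 12 people with at least 10 sessions and all study measures, but not the number enrolled. If 20 had enrolled, and the other 8 were non-completers who were all in the frame, the chance would be C(12, 8)/C(20, 8) = 495/125,970 = 0.004. No firm figure can be given.

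**Conclusion.** The point holds in a narrow form. On the plain reading of the phrase, followed as written, no enrolled person with zero sessions can be interviewed. The reasons for never starting cannot be learned at first hand, and the other feasibility data do not supply them.

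The size is a probability of exactly 0 under the stated rule, and this needs no assumption about the number of non-starters. The figures for a wider frame do rest on one: 20 enrolled and 1 to 4 non-starters. The article does not say that anyone enrolled without having a session; if nobody did, the gap has no practical effect. The other interview topics, the counts, the attrition threshold, the acceptability measures and the depression scores are unaffected.

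**What to change.** **Change the frame.** Draw the same expected 8 interviews from all enrolled participants, at random within three strata: zero sessions, 1 to 9, and 10 or more. Set the allocation so that any non-starters are included, and take everyone in a stratum that is too small to sample. Ask the perceived-benefit questions only of people with at least one session.

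**Or change the question.** If only missed sessions were meant, reword the phrase to say so, and draw no conclusions about non-starters.

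**If the interviews are already done.** The Results section says that the study concluded in May 2024, and the interviews were due one month later. In that case the report should state the frame, give the counts with zero, 1 to 9, and 10 or more sessions, and not generalise interview findings to non-starters.

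**Cost.** Before the interviews, it takes a sentence or two in the protocol and no extra interviews. Non-starters may be harder to reach by telephone. Non-completers would also be over-represented: under the planning figures, taking all 4 of them with 4 completers makes them 4/8 = 50% of interviewees against 4/20 = 20% of those enrolled. The report should say so, since the interviews also inform preliminary efficacy. The exact split between strata is a matter of choice; including the non-starters is not.

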### Potential Limitations

It is conceivable that participants in our study will require a higher level of care than that which can be provided by a CHW. During our regular team meetings, if we determine that a participant requires more mental health support, they will be referred to a local federally qualified health center that provides professional mental health services, albeit through interpreters. All participants will also be counseled in the use of the 2-1-1/9-8-8 crisis line, which has services in Spanish.

Stigma impacts demand for mental health services, and stigma in the LEP Latino population [5] may be a limitation that will affect study participation. We will work closely with our community advisory boards throughout the project to address potential stigma through social media and other messaging to the community.

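### Participant interviews are drawn only from people with at least 1 completed session, so the listed question on why no sessions were completed cannot, read plainly, be answered first-hand by anyone selectable

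*Protocol article*

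**What the plan says.** All the material is in the protocol article, mostly in one paragraph of Data Collection and Analysis.

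- **Purpose.** "The goal of analyzing feasibility is to determine factors that contributed to the implementation of the study". Recruitment and retention are to be assessed, and attrition above 20% is given as an example of a sign of low feasibility. Table 1 lists qualitative interviews with thematic analysis against feasibility. The text adds counts of people who express interest, enroll and complete.
- **Who is interviewed.** Both CHWs and a subset of participants, with 8 expected, one month after the study concludes. For the participants the rule is: "Participants who complete at least 1 session will be randomly selected by a research assistant".
- **What is asked.** The potential questions include what helped or hindered participation, "including reasons for not completing any sessions".
- **Second use of the interviews.** The article also uses them for preliminary efficacy, asking about the effect on mood and depression.
- **Context.** In the Participants section: "The study enrollment goal will be 20 with an anticipated attrition rate of 20%, for a final n=16", and "Participants who complete 10 of the 12 sessions will be considered to have completed the interventions". Participants schedule their own sessions with the CHW and need not meet weekly.

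The article describes no other interview route to an enrolled person with zero sessions.

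**The concern.** The selection rule and the question do not fit each other. A person who has completed at least 1 session cannot explain at first hand why they completed none, and a person who completed none cannot be drawn. This comes from the sampling frame itself. It does not depend on how many interviews are held or on which people a random draw happens to pick.

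The point matters because feasibility is a stated aim and the interviews are the part of the plan that can explain the counts. The counts can show that someone enrolled and did not complete, but not why. If some enrollees never start, the barriers reported will come only from people who got past the first one. Listing the topic suggests that the authors wanted this information, so this is a conflict between two statements in the article and not a detail left to a fuller document.

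**Working it through.** The article gives no figure for this point, so the check is mainly one of logic.

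**Step 1. Sort enrollees by sessions completed, using the article's own definitions.**

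| Sessions completed | In the enrolled count | In the completed count (at least 10 of 12) | Can be drawn for interview (at least 1) | Can say first-hand why no session was completed | Can describe the effect of the intervention |
|---|---|---|---|---|---|
| 0 | yes | no | **no** | **yes** | no |
| 1 to 9 | yes | no | yes | no | yes |
| 10 to 12 | yes | yes | yes | no | yes |

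**Step 2. Compare the two sets.** Selectable = {sessions ≥ 1}. Able to answer first-hand = {sessions = 0}. The overlap is empty, so the number of selectable people who can answer is 0 whatever the enrollment, the attrition or the draw.

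**Step 3. See what still captures the zero-session group.** They are in the enrolled count and not in the completed count, so the comparison of attrition with 20% is unaffected. The CHWs, with whom participants schedule their sessions, are interviewed and may have an impression of why someone did not begin. Neither source gives the participant's own reasons.

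**Step 4. Bound the size on the plan's figures.**
- Anticipated losses: 20 × 0.20 = 4. Remaining: 20 − 4 = 16, which reproduces the stated final n.
- Let k be the number of those 4 who complete no session. The article does not give k. The share of anticipated losses with no first-hand explanation is k/4:

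| k | 0 | 1 | 2 | 3 | 4 |
|---|---|---|---|---|---|
| k/4 | 0% | 25% | 50% | 75% | 100% |

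These percentages restate an assumed k and are not an estimate. All that follows from the article is the range, 0 to all of about 4 people.

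**Step 5. Test the looser reading.** If the topic means any sessions that were missed, then everyone with 1 to 11 sessions can be drawn and can answer. The mismatch disappears, but the reasons of people with zero sessions are still not collected, and the article does not say so.

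**The case against.** The strongest case on the other side has five parts.

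1. **The wording may mean missed sessions.** Sessions are self-scheduled, need not be weekly, and 10 of 12 counts as completion, so missed sessions among starters are expected and those people are in the frame. This is a possible reading and it lowers confidence in the contradiction. The plain sense is still zero sessions, and if the looser sense was meant the phrase needs rewording.

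2. **Only the frame is a rule.** The topic is a parenthesis in a list of potential questions, and the actual guide is not shown. This stands: it is a mismatch between a rule and an intended topic, not two rules in conflict.

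3. **The frame has a reason.** The same interviews ask what effect the intervention had, which requires exposure. With about 8 interviews, a draw from exposed participants is defensible. This also stands, and it is why the draw should be kept and supplemented.

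4. **Non-starters are not invisible.** The counts include them and the CHWs can speak about them. A reader might infer that the plan can never learn anything about why people did not start, or that its feasibility assessment rests on interviews alone. The article supports neither. What is missing is the participants' own account.

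5. **The bias is not shown.** A reader might infer that stigma is the expected barrier, that it shows most among people who enroll and never begin, and that barriers are therefore understated. Potential Limitations says only that stigma "may be a limitation that will affect study participation". It does not mention enrollees who never start, and stigma could equally stop people before enrollment, where interviewing all enrollees would not reach them.

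A reader might also take the reported 12 completers as evidence of many non-starters. Actual enrollment is not reported. Even if 20 had enrolled (an assumption), the remaining 20 − 12 = 8 could all have completed at least one session.

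**Conclusion.** The point holds in a limited form. On the plain reading, the article poses a feasibility question that no selectable participant can answer first-hand, and it gives no other interview route to enrollees with zero sessions. What is lost is those participants' own reasons for not starting. The counts, the attrition criterion and the Beck Depression Inventory-II analysis are untouched.

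The size is unknown: from nobody to all of the roughly 4 anticipated losses. This assumes that the enrollment goal of 20 and attrition of 20% apply, and that a person with zero sessions counts as lost. If everyone who enrolled completed at least one session, nothing is lost in practice. A claim that uptake barriers are understated by some amount, or that most attrition is unexplained, would go beyond the article. The point merits correction because the remedy is small and serves a stated aim.

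**What to change.** Keep the random draw of about 8 from participants with at least 1 session. In addition:

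- Have the research assistant offer a short interview, on feasibility only, to every enrolled participant with 0 sessions.
- Report those reasons separately, with the number of zero-session enrollees and the number who answered.
- Ask the questions on the effect of the intervention only of those with at least 1 session.

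If only missed sessions or early stopping was meant, reword the topic accordingly and state that the reasons of enrolled non-starters are not represented.

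The cost is a sentence or two in the protocol and a few extra calls by a research assistant already in the plan. Non-response among non-starters is likely, and their interviews say nothing about the intervention's effect. The article reports that the study concluded in May 2024 and that analysis took place in August 2024. If the interviews are already closed, what remains is to report how many enrollees completed no session, state the limitation, and correct the frame for the larger-scale projects mentioned under Expected Impact.

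### No end-of-study BDI-II is scheduled for anyone who stops before 10 sessions, so the pre-post change is a completer result, and assessments fall at differing elapsed times

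*Protocol article*

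**What the plan says.** Data Collection and Analysis gives the BDI-II schedule: "at baseline, after 3 sessions, after 6 sessions, after 9 sessions, and upon completion of the BA intervention". Participants defines completion: "Participants who complete 10 of the 12 sessions will be considered to have completed the interventions". No BDI-II is stated at withdrawal, after stopping, or at a fixed date. The only later contact that can include non-completers is a qualitative telephone interview with a random subset (expected n=8) of those with at least one session, and no BDI-II is mentioned there.

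On pacing, Intervention says "The trained CHWs will deliver a 12-week program of BA over the phone", while Participants says "Participants will schedule their own sessions with the CHW and do not have to meet weekly". No maximum duration is given.

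On analysis, the abstract says "Preliminary efficacy will be tested in pre- and postscores of the Beck Depression Inventory and semistructured interviews". Data Collection and Analysis says "We will use repeated measures ANOVA to estimate the trends or changes in depression scores over treatment", and Table 1 lists "Linear regression with repeated measures". On numbers, Participants says "The study enrollment goal will be 20 with an anticipated attrition rate of 20%, for a final n=16" and warns that attrition above 20% may bring attrition bias. Results reports 12 people with at least 10 sessions and all measures, without saying how many enrolled.

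**The concern.** The measurement schedule follows treatment, so stopping treatment also stops measurement. The people whose outcome is most in doubt are then the ones without a final score. A pre-post comparison can include only those who stayed, and in a single-arm pilot there is no second group against which to judge that selection.

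The schedule also counts sessions, not weeks. With self-booked sessions, two people at the same nominal assessment may be at quite different times from baseline. A repeated measures analysis that treats them as the same occasion ignores this.

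At stake is the pilot's only quantitative efficacy figure, which is meant to inform larger studies. If it is read as the change expected in everyone enrolled, it may be too favourable.

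**Working it through.** **1. The plan's own figure.** Enrolled 20, attrition 20% (Participants): 20 × (1 − 0.20) = 16. This reproduces the stated final n. There is no power calculation to reproduce.

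**2. Which scores exist, by stopping point** (schedule from Data Collection and Analysis, completion rule from Participants):

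- Stops before session 3: baseline only.
- Stops after 3 to 5 sessions: baseline and after-3.
- Stops after 6 to 8 sessions: baseline, after-3 and after-6.
- Stops after 9 sessions: all but the final score.
- Reaches 10, 11 or 12 sessions: counts as a completer and has a final score.

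**3. How many lack a final score.** At the planned attrition, 20 − 16 = 4 of 20. For the study as run, enrolment N is not stated, so it is an assumption. With 12 completers, the share without a final score is (N − 12)/N:

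- N = 15: 3/15 = 20%
- N = 16: 4/16 = 25%
- N = 18: 6/18 = 33%
- N = 20: 8/20 = 40%

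**4. Possible overstatement.** Let d be the share without a final score, and let non-completers change by a fraction f of the completers' mean change (assumption; the documents give no value). The all-enrolled mean change is the completer mean times (1 − d) + d·f, so the ratio of completer mean to all-enrolled mean is 1/[(1 − d) + d·f].

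- d = 0.20, f = 0: 1/0.80 = 1.25
- d = 0.20, f = 0.5: 1/0.90 = 1.11
- d = 0.40, f = 0: 1/0.60 = 1.67
- d = 0.40, f = 0.5: 1/0.80 = 1.25
- any d, f = 1: 1.00, no overstatement

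**5. Elapsed time.** With mean gap g weeks between sessions (assumption), the score after k sessions falls at about week k × g.

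- After 9 sessions: 9 × 1 = week 9; 9 × 1.5 = week 13.5; 9 × 2 = week 18.
- Final score: from 10 × 1 = week 10 to 12 × 2 = week 24.

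If 12 weeks is a firm limit, the later weeks cannot occur. The article does not say whether it is. The window from October 2023 to May 2024, about 26 to 35 weeks, could hold this spread for early enrollees.

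**The case against.** Several points on the other side stand.

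- **Leavers are not without data.** A reader might infer that anyone who stops early has no outcome at all. The schedule does not support that. Baseline does not depend on sessions, and those who stop after 3 to 9 sessions keep interim scores. A likelihood-based repeated measures model, which the Table 1 entry could cover, can use them under a missing-at-random assumption. That assumption cannot be tested, and people who stop before session 3 have no post-baseline score.
- **Flexible pacing does not confound session number with time.** A reader might infer that it does. Strictly weekly sessions would make the two inseparable; varied pacing allows them to be told apart once dates are used. Confounding with natural recovery comes from having no control group.
- **The sizes rest on assumptions.** The value of f is assumed, and leavers who stopped because they felt better would reverse the bias. Forty per cent attrition is not reported.
- **The 12-week and not-weekly statements can be read together** as a nominal length with flexible booking. What is missing is whether 12 weeks is a limit.
- **This is a small pilot.** Measuring change by sessions received is a legitimate choice, and attrition is itself a feasibility outcome with a 20% criterion.

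It could also be said that early-termination visits belong in a fuller document. That carries less weight here, because the article states a specific schedule and every post-baseline score in it depends on attendance. An analysis plan cannot create scores that were never scheduled.

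**Conclusion.** The point holds in a limited form. No final BDI-II is scheduled for people who stop before 10 sessions, so the pre-post change describes completers unless untestable assumptions are added. At the planned 20% attrition, 4 of 20 would lack the final score. The completer mean would then overstate the all-enrolled mean by 11 to 25%, given the assumed 0 to 50% relative change in non-completers. The 25 to 67% range needs 40% without a final score, that is, 20 enrolled with 12 completers; a reader might take this as what happened, but the article does not report enrolment.

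The same assessment can fall at different elapsed times, for example week 9 to week 18 for the after-9 score under assumed mean gaps of 1 to 2 weeks. The passages on programme length and session frequency should be reconciled.

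This is worth correcting because the remedy is cheap, but it does not invalidate the pilot's feasibility and acceptability aims.

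**What to change.** **For the larger studies this pilot is meant to inform, or any further enrolment:** keep the session-linked scores and add one BDI-II by telephone for every enrolled participant at a fixed time from baseline, whatever their attendance. At the planned numbers this would seek a final score from all 20 instead of 16. A research assistant already makes telephone calls under the plan. State whether the programme has a maximum duration, so that the length and frequency passages agree.

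**For the data already collected** (the study concluded in May 2024, so no fixed-time score can be added now):

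- Report the number enrolled.
- Include all enrolled participants, with their partial scores, in the repeated measures model.
- Use days since baseline, taken from the assessment dates if these were recorded.
- Add a sensitivity analysis that assumes no improvement in those without a final score.
- Label any pre-post change as a completer result.

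**Cost.** In a study of this size, calls to about 4 to 8 non-completers, a date field, one model term, and a small change to the ethics submission. Some calls will not reach people who left, particularly as the $200 payment is tied to at least 10 sessions, so missing final scores will be reduced but not eliminated. Confounding with natural recovery remains, because there is no control group.
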